### Study population

In total, 159 patients aged 50 years or older with a diagnosis of delirium will be included in the study.

#### Inclusion criteria for eligibility

In order to be eligible to participate in this study, a participant must meet all of the following inclusion criteria:

Age over 50 years.Diagnosis of delirium.Richmond Agitation and Sedation Scale (RASS)^45^ score of −2 to +2.Delirium duration of at least 2 days prior to study inclusion, based on delirium assessments and/or descriptions in the medical and/or nursing files.Causes underlying delirium are being treated adequately, as assessed by the treating physician and a panel of delirium experts (ie, psychiatrist, geriatrician and intensivist).

#### Exclusion criteria for eligibility

A potential participant who meets one or more of the following criteria will be excluded from participation in this study:

Inability to conduct valid delirium screening assessment (eg, deaf, blind) or inability to speak Dutch or English.A moribund state.Alcohol/substance abuse withdrawal or stroke as the presumed cause of delirium.Diagnosis of dementia, based on medical record review and/or a score of ≥4.5 on the short form of the Informant Questionnaire on Cognitive Decline in the Elderly.^46^Brain injury of any type (eg, traumatic, vascular, post anoxic) in the previous 6 weeks.One or more contraindications for tACS:Large or ferromagnetic metal parts in the head (except for a dental wire).Implanted cardiac pacemaker or neurostimulator.Skin disease or inflammation at the stimulation sites.History of epilepsy.

#### Inclusion criteria for randomisation

All inclusion criteria are met.Diagnosis of delirium is confirmed using the Delirium Interview^41^ and consultation with a delirium expert who is part of the research team (psychiatrist, geriatrician and/or intensivist).Written informed consent obtained from legal representative.

#### Patient withdrawal

If a patient and/or legal representative wants to withdraw from the study, they can do so without any consequences. We will adhere to the definitions and guidelines stipulated in the code of conduct relating to the expression of objection by incapacitated (psycho)geriatric patients in the context of the WMO (2002). The clinician or investigator can decide to withdraw a subject from the study for urgent medical reasons. There are no expected negative effects of prematurely ending the stimulation sequence.

### Informed consent, randomisation and blinding

For surgical patients, a flyer is provided during the preoperative screening to inform patients and their legal representatives about the study, enabling them to familiarise themselves with this study in advance and consider participation in the event of delirium occurrence. In non-surgical patients, this flyer is provided to the wards with the request to hand this to newly admitted patients. Consultants, including psychiatrists, geriatricians and neurologists, and ward physicians are asked to screen for potential participants. On identification of patients eligible to participate in the trial, consultants and ward physicians inform the research team. The research team will inform the patient and their legal representatives about the study. If the patient and legal representative are possibly willing to participate, the investigator provides the information letter and provides them at least 1 day to consider study participation. If a patient is eligible for study participation, initial informed consent will be obtained from a legal representative, as the patient may be unable to provide consent when delirious (see online supplemental appendix 2 for an example of the consent form). Legal representation is identified using a hierarchical model consistent with local and national laws and regulations. Once patients regain capacity to provide informed consent, they will be asked to provide written informed consent themselves. At any time, the patient or their legal representatives can refuse or withdraw consent for the study without providing a reason and without impacting the treatment provided.

Delirious patients who meet all inclusion criteria but none of the exclusion criteria for eligibility and randomisation will be randomised to one of the study arms. Randomisation will be conducted electronically via the Castor Electronic Data Capture (EDC) study management system (Castor, Ciwit B.V., Amsterdam, the Netherlands), using a validated block randomisation model, stratified by study centre. In the pilot phase, standardised active tACS and sham carry equal weight (1:1). Patients will be randomised with block sizes of 2 and 4. In the main study phase, four groups will be created in Castor EDC (standardised active, personalised active, standardised sham, personalised sham) with different weights, depending on the number of participants who have been randomised to the active and standardised sham groups during the pilot phase. As the first 30 patients are included during the pilot phase, randomisation weights will be 3, 4, 1 and 2, respectively. These numbers are chosen to closely match the overall 1:1:1 allocation. Randomisation will be performed with block sizes of 10 and 20, which are randomly selected.

Following randomisation, a designated study team member not involved in any other study procedures or data analysis will be aware of the randomisation outcome. This person will have access to a list of codes that permits the tACS device to deliver active or sham stimulation. Participants and all other study staff will be blinded to whether active or sham stimulation is applied. To ensure blinding during the intervention, the monitor displaying the raw ECG traces will be covered with cardboard paper before the start of the procedure for patients on continuous ECG monitoring. Due to the additional EEG required in the personalised treatment arm, blinding with regard to receiving standardised or personalised tACS will not be possible. However, EEG preprocessing and data analysis will be performed blinded for treatment allocation.

### Intervention

tACS will be administered to participants who are randomised using the Nurostym tES device (Brainbox, UK) by a trained member of the study team. The same tACS device and settings will be used across all three participating centres to ensure consistency of results. For all study arms, tACS will be administered at an intensity of 2.0 mA (peak to peak) for 30 min using two 5×5 cm saline-soaked electrodes while the impedance is kept below 10 kΩ. Electrode placement (described below) follows the 10–10 EEG system, ensuring consistent positioning of tACS electrodes across different stimulation days, patients and centres. The electrodes will be positioned beneath a 64-channel EEG cap. During the first treatment session, this cap will also be used for repeated EEG measurements, whereas on subsequent treatment days, it will serve solely as a reference for tACS electrode positioning. Treatment with psychoactive medication(s) that is deemed necessary for the participant will be continued as prescribed by the treating physician.

#### Standardised tACS

Standardised tACS will be applied with a frequency of 10 Hz, which is in the alpha frequency and is consistent with other alpha-tACS studies.^47^ The tACS electrodes will be positioned over AFz and Oz, according to the 10–10 system for electrode placement (figure 2). This electrode placement results in the generation of electrical fields in brain areas that demonstrate altered connectivity in delirium, including the dorsolateral prefrontal cortex, precuneus and posterior cingulate cortex.^22 23^ At the beginning of stimulation, the intensity will ramp up for 30 s to 2.0 mA peak to peak, while at the end of stimulation, the intensity will ramp down for 30 s to 0 mA.

**Figure 2 F2:**
[figure not shown]
Standardised approach for applying transcranial alternating current stimulation (tACS). (A) Representation of the electrode placement. Two 5×5 cm electrodes will be positioned over AFz (anterior) and Oz (posterior) locations, indicated by coloured squares (blue for posterior, yellow for anterior). (B) Visualisation of the electric field distribution in the brain during tACS with an intensity of 2 mA (peak to peak). The colour map represents the magnitude of the electric field (magnE), measured in volts per metre (V/m). SimNIBS software (version 4) was used for simulation.^56^

#### Personalised tACS

For personalised tACS, settings will be based on a computational model for delirium and a virtual trial. To achieve this, this study will use a computational model capable of mimicking in silico the EEG findings that have been observed in delirium. A network of neural masses with each neural mass (ie, the smallest subsection of the network) representing a population of excitatory and inhibitory neurons in the brain will be used. By modifying the excitatory-inhibitory balance and/or subcortical input to the neural masses, different pathologies can be simulated. The model generates multiple channel EEG-like output, allowing for quantitative analysis of outcomes of different model parameters. Model parameters will be manipulated to simulate neuronal/synaptic changes during delirium as well as individual (personalised) brain activity and functional connectivity, resulting in EEG characteristics that are similar to that observed in a particular patient, amounting to a personalised disease model. Thereafter, the effect of various tACS parameters will be simulated to counter delirium mechanisms. These strategies will differ with regard to the electrode location and stimulation frequency. The different quantitative measures resulting from the model will be analysed similarly to patient EEG data, predicting which electrode placement and stimulation frequency will result in the most optimal treatment response regarding power spectrum and connectivity characteristics. In this context, optimal treatment response is defined as a change of spectral and connectivity characteristics of the model output in the direction of a healthy state. The optimal, individualised tACS protocol will thereafter be applied as personalised delirium treatment. Settings will be determined once during the first session and will remain unchanged in remaining sessions. All patients in the active treatment arm will receive tACS with an intensity of 2.0 mA (peak to peak) and a stimulation duration of 30 min.

We are currently investigating the optimal way to fit a network of neural masses to an individual patient with delirium, allowing performance of a virtual trial with the specified outcome parameters. In this phase, several strategies will be considered: a disease model tailored at multiple dimensions to the individual neurophysiology,^48^ a model tailored to the individual peak frequency^49^ or spatial modelling of individual brain activity. The results of this development process will be published in a separate paper describing the details of this approach and the most effective strategy will be used in the second phase of the trial.

#### Sham stimulation

The procedure for sham stimulation will be identical to either standardised or personalised tACS, except for the electrical current administered. After the 5-digit pin code is entered, which enables sham stimulation, the tACS device will ramp up to 2.0 mA peak to peak for 30 s, stimulate for 60 s and ramp down for 30 s to 0 mA. This mimics the perception of actual tACS stimulation and improves blinding. To evaluate the effectiveness of blinding, both the participant and the researcher will be asked to guess the group allocation after the first and last treatment session (online supplemental appendix 1).

### Outcomes

#### Pilot study outcomes

During the pilot phase, data regarding the percentage of fully completed tACS sessions will be recorded as well as increased care requirements within 1 hour following tACS administration. An increase in care requirement is defined as a (medication-based) intervention (eg, for heightened agitation or skin issues resulting from the electrodes), fixation, or transfer to unit with more advanced care (eg, the intensive care unit). Furthermore, duration of delirium will be recorded as defined in the secondary outcomes below. On analysis of these findings, adjustments to the protocol may be proposed and will be submitted to the Medical Research Ethics Committee (MREC) for approval before the start of the main study phase, if deemed necessary.

#### Main study primary outcome

##### Relative delta power

An 18-min resting state EEG recording will be conducted by a trained clinical researcher directly before and after the first tACS session. EEG recordings will be obtained using a 64-channel Biosemi ActiveTwo EEG system with active gel electrodes (Biosemi B.V., Amsterdam, Netherlands) at a sampling rate of 2048 Hz. Active electrodes, wherein each electrode has its own amplifier, are employed to reduce artefacts due to enhanced signal-to-noise ratio. EEG data will be visually inspected for eye movement and muscle artefacts. A minimum of 80 s of eyes closed artefact-free data will be analysed. Data will undergo FIR bandpass filtering in the following frequency bands: delta (0.5–4 Hz), theta (4–8 Hz), alpha (8–13 Hz), low beta (13–20 Hz) and high beta (20–30 Hz). Relative delta power will be calculated by dividing the total power within the delta frequency band (0.5–4 Hz) by the total power across frequency bands from 0.5 to 20 Hz. The upper limit of the frequency band is limited to 20 Hz to reduce the impact of muscle artefacts and high-frequency noise on the relative delta power calculation.^50^

##### Secondary outcomes

Delirium duration assessed by the number of days with delirium during the treatment period (up to 14 days). A delirium-positive day is defined as having an Intensive Care Delirium Screening Checklist (ICDSC)^51^ score of ≥4. A score of –4 or lower on the RASS followed by an ICDSC score ≥4 is counted as a delirium day. For days where ICDSC is missing (eg, due to limited staff availability on some weekends), days with a Delirium Observation Screening Scale (DOSS)^52^ score ≥3 will also count as a delirium day. The DOSS is administered as standard of care.Delirium severity as assessed by the cumulative ICDSC score per participant recorded on days with delirium during the treatment period. In instances where ICDSC scores are unavailable, scores will be estimated using information from the electronic patient record.Quantitative EEG measures include peak frequency, spectral analysis and connectivity measures such as the phase lag index,^53^ corrected amplitude envelope correlation^48^ and topological measures based on the minimum spanning tree.^54 55^Length of hospital stay as assessed by the total number of days admitted to the hospital.Cognitive status 3 months after the first tACS session as assessed by the TICS-M.^43 44^Presence and duration of sensations related to tACS treatment including tingling sensations, itching, mild transient redness of the skin and discomfort on the region of stimulation with the sensation questionnaire developed for this study (online supplemental appendix 1).The treatment burden, perception of receiving either sham or active tACS and patients’ perceptions of the therapeutic relationship with the researcher(s) will be evaluated using the questionnaires on feasibility, or blinding and subjective treatment experience, which have been developed for this study (online supplemental appendix 1).

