### Study design and setting

This study is a double-blind, RCT conducted across three medical centres in the Netherlands: the University Medical Center (UMC) Utrecht, Radboud UMC and HagaZiekenhuis. To assess safety and feasibility of tACS in delirious patients, the study will start with a pilot phase in which 30 patients will be randomised in a 1:1 ratio to receive daily either standardised active tACS or sham treatment for a maximum of 14 days, or until resolution of delirium or hospital discharge.

On completion of the pilot phase, the main study phase will begin, introducing the personalised treatment arm. Criteria for continuing to the main study phase are defined under outcomes. All patients from the pilot phase will be included in the main study analyses. Randomisation weights will be recalculated, and participants will be allocated in an overall 1:1:1 ratio to receive either standardised tACS, personalised tACS, or sham treatment (ie, combining personalised sham and standardised sham tACS into one arm). The baseline visit will include delirium assessment using the Delirium Interview,^41^ administered by a trained researcher, and reviewed by an expert delirium panel. Furthermore, information will be collected from the electronic patient record and the Clinical Frailty Scale^42^ will be evaluated. After these assessments, the first treatment session starts which includes a 64-channel EEG measurement before and after the first tACS or sham treatment. Also, a questionnaire on sensation to assess possible adverse events (AEs) of tACS, a questionnaire on feasibility and questionnaire on blinding and subjective treatment experiences (online supplemental appendix 1) will be administered. Following this, daily tACS or sham treatment visits and delirium assessments will take place for a maximum of 14 days, or until resolution of delirium or hospital discharge, whichever comes first. To account for fluctuations in delirium symptoms, resolution of delirium is defined as two consecutive negative delirium assessments. The treatment phase will end with a close-out visit including a follow-up 64-channel EEG and administration of the questionnaires on sensation, blinding and subjective treatment experiences. A brief cognitive assessment using the Telephone Interview for Cognitive status, modified version (TICS-M)^43 44^ is planned at 3 months after the first tACS session. The study design is illustrated in figure 1, and the study schedule is presented in table 1.

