
**Figure 1 F1:**
[figure not shown]
Study flow chart. EEG, electroencephalography; tACS, transcranial alternating current stimulation; T, treatment; V, visit.

**Table 1 T1:** Overview study procedures

Procedures (time needed)	Baseline visit (V1)	First treatment visit (T1)	Additional treatment visits (T2 up to T14)	Post-treatment visit (V2)	Follow-up visit (V3)
Medical history*	X				
Physical health*	X				X
Current medication use*	X	X	X	X	X
Clinical Frailty Scale*	X				
Sensation questionnaire (5 min)		X		X	
Blinding and subjective treatment experience (1 min)		X		X	
Feasibility questionnaire (5 min)		X			
Delirium interview (10 min)	X				
ICDSC (10 min)	X	X	X	X	
DOSS (5 min)†	X	X	X	X	
TICS-M (10 min)					X
EEG (40 min)	X‡	X		X	
tACS (30 min)		X	X		
Estimated total duration	25 or 60 min‡	95 min	45 min	65 min	15 min

* This information will be recorded as part of standard clinical care, and missing information will be requested via family and will therefore not require additional time.

† Only non-intensive care unit () patients will be assessed using the DOSS.

‡ Only the group randomised to personalised tACS will receive an EEG during the baseline visit.

DOSS, Delirium Observation Screening Scale; EEG, ElectroencephalogramICDSC, Intensive Care Delirium Screening Checklist; tACStranscranial altering current stimulationTICS-M, Telephone Interview for Cognitive status, modified version

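### Delirium duration has no rule for death or discharge while delirious, so such exits score as short delirium and, if they differ by arm, can favour the worse arm

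*Protocol article*

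**What the plan says.** All references are to the protocol article.

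- **Duration** (Secondary outcomes): "Delirium duration assessed by the number of days with delirium during the treatment period (up to 14 days". A positive day is an ICDSC score of 4 or more, with a DOSS fallback where the ICDSC is missing.
- **Severity** (same section): "Delirium severity as assessed by the cumulative ICDSC score per participant recorded on days with delirium during the treatment period".
- **Window** (Study design and setting): "delirium assessments will take place for a maximum of 14 days, or until resolution of delirium or hospital discharge, whichever comes first". Discharge is listed apart from resolution, and "resolution of delirium is defined as two consecutive negative delirium assessments". Leaving hospital while still delirious is therefore an exit that the design foresees.
- **After the window** (Table 1): the post-treatment visit has the ICDSC and DOSS. The 3-month visit has the TICS-M but no delirium assessment.
- **Unresponsive days** (Secondary outcomes): "A score of –4 or lower on the RASS followed by an ICDSC score ≥4 is counted as a delirium day".
- **Death**: it appears as a criterion for a serious adverse event (Safety reporting). No section gives it a value, a rank or a censoring rule in the duration or severity score.
- **Tests**: Statistical analysis assigns functional outcomes to parametric or non-parametric tests according to their distribution. Interim analysis compares duration between active and sham after the pilot by a t-test or Mann-Whitney test, and the results go to the ethics committee before the main phase.

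**The concern.** A count of bad days is a sound outcome only if everyone is observed for the same time, or if the reason for stopping is scored. Here observation stops for three quite different reasons (recovery, discharge while delirious, death), and the count treats them alike. Fewer days reads as better, so the two unfavourable exits are rewarded. A rank test does not help, because an early death takes a low, and hence good, rank.

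The rule for deeply unresponsive days works in the same direction. As worded, such a day counts only if a positive ICDSC follows, so unresponsive days that end in death add nothing.

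Duration is the first secondary outcome listed, and the Introduction gives its link with long-term cognition as a reason to seek treatment. It is also one of the three comparisons made between the pilot and the main phase. A result in the wrong direction would therefore matter, although the primary EEG outcome is not touched.

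**Working it through.** The document prints no figure for duration or severity, so there is none to reproduce. The check has three parts.

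**1. From the definitions alone**

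| Course | Duration | Cumulative ICDSC |
|---|---|---|
| Delirious 3 days at ICDSC 8, then dies or is discharged delirious | 3 | 3 × 8 = 24 |
| Delirious 3 days at ICDSC 8, then recovers | 3 | 3 × 8 = 24 |
| Delirious 8 days at ICDSC 4, then recovers | 8 | 8 × 4 = 32 |

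The first two courses cannot be told apart. The first scores better than the third on both outcomes.

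**2. Effect of mortality alone**

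Assumptions, none from the document: delirium duration is geometric with mean 6 days (daily continuation q = 5/6), capped at 14. A proportion p dies on a day uniform over 1 to 14. Treatment has no effect on delirium.

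- Mean count without death: (1 − q^14)/(1 − q) = 5.53 days.
- Mean count among those who die, averaging (1 − q^D)/(1 − q) over D = 1 to 14: 4.02 days.
- Planned mean at p = 5%: 0.95 × 5.53 + 0.05 × 4.02 = 5.46.
- Planned mean at p = 20%: 0.80 × 5.53 + 0.20 × 4.02 = 5.23.
- The arm with more deaths looks 5.46 − 5.23 = 0.23 days better.
- Days alive and delirium-free to day 14, death scored 0: 0.95 × (14 − 5.53) = 8.04 v 0.80 × (14 − 5.53) = 6.77. That arm is 1.27 days worse.

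For scale, the SD of the capped count in this model is about 4.1 days. With 53 per arm the standard error of a difference is 4.1 × √(2/53) ≈ 0.8 days, so the shift is a little over a quarter of one standard error.

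**3. Death and discharge while delirious together**

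Assumptions: each delirious day ends in resolution with probability r (equal in both arms), in exit while delirious with probability e, or in continuation. Put s = 1 − r − e.

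- Expected counted days: (1 − s^14)/(1 − s).
- Expected days alive and delirium-free, exit while delirious scored 0: sum over k = 1 to 14 of s^(k−1) × r × (14 − k).

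Example at r = 0.10: (1 − 0.88^14)/0.12 = 6.94 at e = 0.02, and (1 − 0.85^14)/0.15 = 5.98 at e = 0.05.

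| r | Counted days, e = 0.02 v 0.05 | Arm with more exits looks shorter by | Delirium-free days, e = 0.02 v 0.05 | That arm is worse by |
|---|---|---|---|---|
| 0.10 | 6.94 v 5.98 | 0.96 | 5.88 v 5.35 | 0.54 |
| 0.15 | 5.45 v 4.78 | 0.67 | 7.54 v 6.91 | 0.63 |
| 0.20 | 4.41 v 3.93 | 0.48 | 8.72 v 8.06 | 0.67 |

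(Differences are taken before rounding.)

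At r = 0.10 the proportion who resolve is r times the counted days: 69.4% v 59.8%. At an assumed constant ICDSC of 5, mean cumulative ICDSC is 5 × 6.94 = 34.7 v 5 × 5.98 = 29.9. This too favours the arm in which fewer recover.

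With r equal in both arms, a larger e makes s smaller, and every term of the sum that gives the counted days shrinks. In this model the direction therefore does not depend on the rates chosen. The size does.

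**The case against.** - **The bias needs exits that differ by arm.** Participants and staff are blinded to active or sham stimulation, which limits differential discharge decisions, and moribund patients are excluded. This stands as a reason to expect a small effect. It does not supply a rule for the exits that do occur.
- **The size is small and rests on assumed rates.** This stands. Part 2 needs mortality to quadruple to move the mean by about 0.2 days. The larger gaps in part 3 pool discharge with death and imply that 13.9% v 29.9% leave while delirious at r = 0.10 (e times the counted days).
- **Deaths would be seen as serious adverse events.** Those up to 24 hours after the last session meet the definition. A reader could then see an imbalance beside the score, but the score itself would be unchanged.
- **Handling of competing events is often left to an analysis plan.** This is true of method. Here the outcome and its window are fixed in the article, and an analysis plan could repair them only by changing or supplementing what is stated.

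Two stronger readings are tempting and are not supported:

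- Table 1 restricts the DOSS to patients outside intensive care, so a reader might infer that missing ICDSC days in intensive care count as delirium-free. No sentence says so. Secondary outcomes also provides for unavailable ICDSC scores to be estimated from the patient record. That provision is written under severity, so its reach to duration is unclear, but this is no more than an ambiguity.
- A reader might say that cumulative ICDSC does not measure severity, since 10 days at 4 (40) outranks 4 days at 8 (32). A declared burden score does exactly that. Replacing it with a mean per assessed day would still not penalise death: 3 days at 5 and 14 days at 5 both score 5.

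**Conclusion.** The point holds for duration, and the cumulative ICDSC score inherits the same truncation. As defined, both outcomes give death or discharge while delirious the same credit as early recovery, and the planned t or rank comparison can then favour the arm with more such exits.

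The size cannot be fixed from the document, which gives no rate of death or of discharge while delirious. Under the stated assumptions it is about 0.2 days for mortality of 5% v 20%, and 0.5 to 1.0 days for daily exit of 2% v 5%, against a standard error near 0.8 days.

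It would be going too far to infer that the trial will report harm as benefit. That requires exits that differ by arm, and nothing in the document shows that they will. These are secondary outcomes and the primary EEG analysis is unaffected. The change should be made, but the trial does not stand or fall by it.

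**What to change.** 1. Analyse delirium duration as days alive and free of delirium through day 14 after the first session. Score death before day 14 as 0, the worst value.
2. Assign days after discharge by delirium status at the last assessment, with a sensitivity analysis that varies this assignment.
3. Compare arms by a rank test or a proportional-odds model, and use the same definition in the post-pilot comparison.
4. Report the numbers of deaths and of discharges while delirious by arm, beside both the duration and the cumulative ICDSC results. The cumulative ICDSC score can stay as defined.

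**Cost:** mainly wording in the protocol or analysis plan, and a composite that needs a sentence of explanation. It is not purely a re-analysis of data in hand. Table 1 gives a delirium assessment at the post-treatment visit, but daily assessment ends at resolution or discharge and serious adverse event capture ends 24 hours after the last session. Vital status to day 14 would therefore have to be recorded for patients who leave or resolve earlier.

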### Statistical analysis

For the analysis of the primary study parameter, a per-protocol analysis will be used. The sole criterion for inclusion in the analysis is that a participant has completed the initial tACS session and EEG recordings. Changes in relative delta power will be assessed using separate linear mixed models for standardised and personalised tACS compared with sham, with relative delta power as the dependent variable, time*group and study centre as fixed factors, and participant as a random factor. Data analysis will be performed blinded for treatment allocation. A significance level of p=0.05 (two-tailed) will be applied. To retain sensitivity to detect potential effects in this novel area of research, no adjustment for multiple comparisons will be made. In cases of deviations from the linear mixed model, robust models and non-parametric alternatives will be considered. Subgroup analysis will be conducted by including additional fixed factors to the mixed models, such as delirium aetiology, sex and age. Functional outcomes, along with other quantitative EEG measurements and cognitive outcomes, will be analysed using non-parametric or parametric tests depending on the distribution of scaled test results. Blinding success for participants as well as researchers will be tested using a χ^2^ test.

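### Delirium is confirmed at entry by interview and expert but counted afterwards by ICDSC of 4 or more, so a confirmed patient who stays below 4 scores zero days and zero severity, which can dilute these secondary comparisons

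*Protocol article*

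**What the plan says.** All references are to the protocol article.

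- **Entry.** Under Inclusion criteria for randomisation, "Diagnosis of delirium is confirmed using the Delirium Interview" and "consultation with a delirium expert who is part of the research team". Under Inclusion criteria for eligibility, the prior course is "Delirium duration of at least 2 days prior to study inclusion", judged from assessments or file descriptions. Neither list sets an ICDSC minimum.
- **Outcome.** Under Secondary outcomes, "A delirium-positive day is defined as having an Intensive Care Delirium Screening Checklist (ICDSC") score of at least 4. For deep sedation, "A score of –4 or lower on the RASS followed by an ICDSC score ≥4 is counted as a delirium day", so that route also needs an ICDSC of 4 or more. The DOSS (3 or more) is a substitute: "For days where ICDSC is missing (eg, due to limited staff availability on some weekends"). Severity is the ICDSC summed over delirium days only.
- **Resolution.** Under Study design and setting, "resolution of delirium is defined as two consecutive negative delirium assessments". No instrument or threshold is named there.
- **Schedule.** Table 1 marks the ICDSC at the baseline visit (V1), the first treatment visit (T1), the later treatment visits and the post-treatment visit.
- **Analysis.** Under Statistical analysis, functional, other EEG and cognitive outcomes "will be analysed using non-parametric or parametric tests depending on the distribution of scaled test results". Under Interim analysis, the pilot comparison of delirium duration uses a t-test or a Mann-Whitney test.

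**The concern.** The condition that brings a patient into the trial is not the condition that is later counted. Someone an expert has just judged delirious can be recorded as having had no delirium at all if the ICDSC does not reach 4. The DOSS cannot correct this, because a recorded low ICDSC takes precedence over it.

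Such patients cannot show benefit on duration or severity. If they occur, they enter every arm as a block of zeros that pulls the arm means together, adds variance and creates ties. Duration and severity are a stated secondary objective, and duration is also compared between arms after the pilot and reported to the ethics committee. A null result on these outcomes could then partly reflect the mismatch of definitions.

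**Working it through.** **Plan's own figure.** There is none for this point. The stated 159 (53 per group) concerns relative delta power. It reproduces as a three-group ANOVA with f = (0.15/0.3)/2 = 0.25, alpha 0.05 and power 80%: N = 157.2, rounded up to 159. The mismatch does not touch it, and no power is claimed for duration or severity.

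**Following one patient through the rules.**
1. Interview and expert confirm delirium, so the patient is randomised whatever the ICDSC.
2. The ICDSC is recorded below 4 on every assessed day: no day counts, and the RASS route does not apply.
3. Days without an ICDSC count only if the DOSS is 3 or more. If none is, the total is 0 days.
4. Severity sums over delirium days only, so it is also 0.

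**Effect on the comparison.** Let q be the share of such patients, equal in all arms. Let the others have mean m0 (sham) or m1 (active), difference d = m0 − m1 and standard deviation s. Then

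- observed difference D = (1 − q)·d
- variance in arm k = (1 − q)·s² + q(1 − q)·mk²
- power ≈ Φ(D/S·√(53/2) − 1.96), where S² is the average of the two arm variances.

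The documents give none of q, m or s. Assume m0 = 5 days, s = 3 and d = 1.5. At q = 10%, D = 0.9 × 1.5 = 1.35. The variances are 8.1 + 0.09 × 25 = 10.35 and 8.1 + 0.09 × 12.25 = 9.20, so S = 3.13 and D/S = 0.432.

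| q | Difference (days) | Standardised effect | Power, 53 per arm |
|---|---|---|---|
| 0% | 1.50 | 0.50 | 73% |
| 5% | 1.43 | 0.46 | 67% |
| 10% | 1.35 | 0.43 | 60% |
| 20% | 1.20 | 0.38 | 49% |
| 30% | 1.05 | 0.33 | 39% |

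Two other assumed sets (mean 6, SD 4, difference 2; mean 4, SD 3, difference 1.5) give 62–63% at q = 10% and 52–54% at q = 20%.

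**Dependence on how misses cluster.** Simulation with 53 per arm, daily resolution 0.15 v 0.25 and a cap of 14 days (all assumed), Mann-Whitney test, about 70% power with no misses:
- *The same patients missed every day:* 10% zero-scored gives about 52% power and 20% gives about 36%.
- *Misses independent from day to day, ICDSC sensitivity 70–90%, no early stopping:* power is 66–67%, because few patients are missed on every day.

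**Remedies under the same kind of simulation.**
- *Adjusting for baseline ICDSC:* costs at most about 1 power point with independent misses. When misses cluster within patients, it gains about 0 to 9 points for duration and 2 to 16 for severity.
- *Restricting to baseline ICDSC of 4 or more:* helps when the same patients are missed every day (36% to 60% at 20% zero-scored). It loses power with independent misses (for example 65% to 48% at 70% sensitivity).

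**The case against.** A diagnostic interview at entry and a short daily scale in follow-up is a common design, there is no directional bias, and the primary outcome is untouched. All of that stands and limits the weight of the point. Covariates for secondary outcomes are commonly left to an analysis plan, which is not shown. That also stands: their absence is not charged as a fault, and the protocol does not say that the tests exclude covariates. The point rests on definitions that the article itself states.

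A reader might infer more than the documents support:

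- **That one low ICDSC gives zero days.** It does not. The outcome counts days, so a patient with a fluctuating course who reaches 4 on any day scores above zero.
- **That such a patient is resolved from the start,** because Table 1 has an ICDSC at both V1 and T1. The resolution rule names no instrument and does not say that V1 counts. The section describes baseline, then the first session, then daily assessments until resolution, so the natural reading applies the rule to the daily course. The text leaves the question open.
- **That dilution is established, at 10–20%.** The documents give no ICDSC sensitivity and no share of low scorers. With independent misses the loss is small.
- **That restricting to baseline ICDSC of 4 or more recovers the lost power.** This holds only if the baseline score picks out the patients who are missed throughout. The Table 1 footnote on the baseline EEG also implies that randomisation falls before or during V1, so the score precedes stimulation but not clearly allocation.

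**Conclusion.** The mismatch is in the text and the point holds in limited form. Entry has no ICDSC minimum, a delirium day needs an ICDSC of 4 or more (or a qualifying DOSS where the ICDSC is missing), and a confirmed patient who never qualifies scores 0 days and 0 severity. This can dilute the duration and severity comparisons, including the pilot comparison of duration, without favouring either arm.

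The size is unknown. It is negligible if such patients are rare or misses are scattered. At 10% zero-scored patients in each arm it is about 10 to 13 power points under the assumed means and SDs, and nearer 18 in the Mann-Whitney simulation (70% to about 52%). All these figures rest on assumptions. The case for acting is that the improvement costs almost nothing.

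**What to change.** 1. **Statistical analysis.** For delirium duration and severity, replace the plain parametric or non-parametric tests with a between-arm model suited to the outcome's distribution, adjusted for the V1 ICDSC score and study centre. The score is already scheduled before stimulation, and centre is the stratification factor.
2. **Optional.** An analysis restricted to V1 ICDSC of 4 or more may be added as a sensitivity analysis only, since it can lose power. If used, state whether the V1 ICDSC is recorded before allocation.
3. **Reconcile three sections.** Study design and setting, Inclusion criteria for randomisation and Secondary outcomes should agree on what makes a delirium assessment negative and whether V1 counts. Which clinical definition applies is for the sponsor to decide.

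The day count itself needs no added rule about when delirium ends, because it has no such component.

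Cost: protocol wording and a slightly richer model. No new data, visits or patients are needed, and the adjustment cost at most about 1 power point in the least favourable case simulated.
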